## Methods

### Study aims and design

The overall aim of the study is to assess if detection of hypoxaemia, and/or severe pneumonia in children 0–59 months by LHWs during their monthly home visits will increase hospital referral acceptance among families in district Jamshoro, Sindh, Pakistan.

Primary objectives are:

To assess and compare the impact of ‘pulse oximetry’ used by LHWs at household level on increasing hospital referral acceptance rates in intervention clusters (district Jamshoro) for children aged 0–59 months with severe pneumonia with the impact of LHWs using clinical signs alone in non-intervention clusters of the same district.To investigate the likely predictors (demographic, clinical) of hospital referral acceptance in both the groups.

Secondary objective is:

To compare clinical outcomes (treatment completion, treatment failure, hypoxaemia) of children 0–59 months who accepted referral to those who refused admission and were treated at home.

A community-based cluster randomised trial will be conducted in district Jamshoro, among children of ages 0–59 months (figure 1). In intervention areas, all children with cough, fever or difficulty in breathing (acute respiratory illness) will be assessed for study eligibility (signs and symptoms of severe pneumonia, or hypoxaemia alone, or severe pneumonia with hypoxaemia) by LHWs during their monthly home visit in their catchment area. In control areas, study eligibility will require detection of signs of severe pneumonia alone (online supplemental appendix 1) during LHW monthly visits. Data will be collected on demographics, likely predictors and clinical outcomes using a structured questionnaire.

10.1136/bmjopen-2020-046158.supp1Supplementary data

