**Figure 1 F1:**
[figure not shown]
Trial profile. LHW, Lady Health Worker, PO, Pulse Oximetry.

The primary outcome is hospital referral acceptance in children under 5 with severe pneumonia and to identify demographic and clinical predictors of hospital referral acceptance. The predictors will include distance of child home to referral facility, socioeconomic status of household, parental education, child age, nutritional status, respiratory rate, temperature, hypoxaemia and presence of other illnesses.

Secondary outcomes include duration of oxygen therapy, treatment failure, duration of hospital stay, vital and health status of child at day 7th and 14th.

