### Participant

Any child aged 0–59 months having signs and symptoms of acute respiratory illness (cough, fever, difficulty in breathing) in intervention clusters will undergo assessment of (1) signs and symptoms of severe pneumonia and (2) pulse oximetry during monthly LHW home visits. Presence of severe pneumonia with or without hypoxaemia, or hypoxaemia alone will merit hospital referral (non-facilitated). Any child aged 0–59 months having signs and symptoms of acute respiratory illness (cough, fever, difficulty in breathing) in control clusters will undergo assessment of (1) signs and symptoms of severe pneumonia alone. Presence of severe pneumonia will merit hospital referral (non-facilitated). Exclusion criteria will include lack of consent and, non-availability (lost to follow-up, migration) on days of scheduled follow-up visits (days 7 and 14). Those who accepted referral but did not show up at hospital will be included in final analysis.

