### Training of LHWs

The LHW programme of Pakistan consists of a community-based group of first-level health workers with the principal mandate of home-based maternal and child health. The recruitment process is well defined and selection criteria include: at least 8 years of education with middle school pass, local residency, recommendation from the community and preferably married.^32^ Once selected, they receive 15 months of basic training in mid-wifery and family planning using standardised training manuals and curriculum, and periodic refresher training courses. Each of these LHWs is typically responsible for approximately 1000 people, or 150 homes, and often serve as the primary healthcare contact in these rural communities.^32 33^

We chose LHWs as study personnel due to their access to homes on regular monthly basis. We trained intervention and control LHWs in separate groups for all of the following: (1) classification of ARI (no pneumonia, pneumonia, severe pneumonia) using standard acute respiratory infections training modules (WHO and IMNCI), (2) identification of danger signs and (3) case management of pneumonia at home with oral amoxicillin and severe pneumonia with stat dose of antibiotic before hospital referral. Intervention LHWs received an additional training in using a pulse oximeter and obtaining a valid reading. The principal investigator (PI) led these training sessions with senior trainers of the LHW programme (lady health supervisors).

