#### Procedure at referral facility

Children who accept hospital referral in both intervention and control clusters and reach hospital premises with LHW referral slip will be assessed by study physician at the referral centre. An SMS notification with brief details of referred child will have been provided to trained study personnel (study physician) in advance at time of referral at both the referral facilities. Children with severe pneumonia and/or hypoxaemia as per LHWs who reach referral hospital premises will be examined and subjected to pulse oximetry again by the study physician at referral facility. If signs and symptoms of severe pneumonia are present, the child will be admitted for further appropriate treatment (oxygen therapy via nasal or nasopharyngeal route and intravenous antibiotics, etc) and if the symptoms are not severe (absence of danger sign), the child will be treated in outpatient care as per the standard of referral facility. All the children admitted at referral facility will undergo 12 hourly monitoring by study personnel and filling of CRF and hospital physician form (HPF) at days 1, 7 and 14. Those children who refused the referral will be visited by study community health workers after 24 hours to confirm referral refusal and to fill CRF.

Preliminary meetings will be held with the executive director health Jamshoro, director general health Sindh, in-charge LHW programme Sindh and in-charge paediatric units LUMHS to ensure their cooperation through study duration. Emergency and paediatric unit staff at the referral facilities along with study personnel (physician/nurse) will be trained on management of severe pneumonia according to the integrated management of neonatal and childhood illnesses (IMNCI) guidelines.^34^ A baseline survey will be conducted at the health facilities to ensure availability of oxygen and necessary intravenous antibiotics. Even though it is ideal to guarantee sustainable oxygen systems at the two chosen referral public sector hospitals, this study does not provide oxygen, and therefore, aims to assess ‘real-life’ situations in public hospitals and their impact on severe pneumonia outcomes with or without hypoxaemia. LHWs will be incentivised on basis of their contribution to the study activities.

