### Data analysis

The primary analysis for each outcome will perform on an ‘intention-to-treat’ basis, that is, all children included in the analysis who were enrolled in the study according to the group to which they were allocated. All analyses will account for the cluster randomised design to ensure correct type I error rates and CIs.^35^ Baseline characteristics will be compared by analysing differences in means and proportions among the study arms. Categorical outcomes will be compared using χ^2^ test and continuous outcomes using Student’s t-test. For analysis of predictors of referral acceptance, generalised linear model will be used with logit link function. The univariate analysis will be conducted to explore the independent effect of each predictor on outcome. The variables significant at a liberal p<0.20 will be included in multivariate model for adjustment. The results will be reported as relative risk with 95% CI. Type 1 error will be set at 5% level. All analysis will be done using STATA V.15.

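### Hypoxaemia is planned as a predictor of referral acceptance in both arms, but in control clusters the only described SpO2 reading exists once the family has already accepted, so its association with acceptance cannot be estimated there

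*Protocol article*

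**What the plan says.** The second primary objective, under Study aims and design, is "To investigate the likely predictors (demographic, clinical) of hospital referral acceptance in both the groups". The outcomes paragraph after the Figure 1 caption names nine predictors: distance to the facility, socioeconomic status, parental education, and "child age, nutritional status, respiratory rate, temperature, hypoxaemia and presence of other illnesses".

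The article describes SpO2 being measured at two points:

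- **At home, intervention clusters only.** The Participant section gives the second part of the intervention assessment as "2) pulse oximetry during monthly LHW home visits". Children "in control clusters will undergo assessment of (1) signs and symptoms of severe pneumonia alone". The section on training of LHWs agrees: "Intervention LHWs received an additional training in using a pulse oximeter and obtaining a valid reading".
- **At hospital, both arms.** Under Procedure at referral facility, referred children "who reach referral hospital premises will be examined and subjected to pulse oximetry again by the study physician".

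Families who refuse are visited by community health workers after 24 hours, to confirm the refusal and complete a form. Enrolled children are seen again on days 7 and 14. No oximetry is described at these visits.

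The strengths and limitations box defines acceptance as verbal agreement together with a hospital visit. The Data analysis section plans a generalised linear model with a logit link for the predictors, preceded by univariate screening.

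**The concern.** In the control arm the predictor is observed through the outcome. A control child acquires an SpO2 value by reaching hospital, and reaching hospital is part of what counts as acceptance. A control family that refuses, or agrees and never arrives, leaves no value.

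This is not ordinary missing data. With no value in any control non-accepter, nothing in the control data shows how common hypoxaemia was among them. Imputation could fill the gap only with an assumption that cannot be tested.

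What is at stake is a named primary objective for the clinical variable most central to this trial. There is also a risk to the other eight predictors: if hypoxaemia sits in the same multivariable model, the children without a value drop out of that model altogether.

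**Working it through.** **Inputs**

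- Total of 4,160 children; 10% acceptance in controls and 15% with oximetry (Sample size section).
- 1:1 allocation (Randomisation and masking), applied to children as 2,080 per arm.
- Acceptance of 8% to 23% reported for facilitated referral of sick young infants, and community hypoxaemia prevalence of 16% to 39% (both from the Introduction). These are used only to show ranges.

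The total is taken as stated. It does not reproduce from its own inputs. With a two-sided 5% level and 90% power, 10% against 15% needs 918 per arm, or 1,836 in total. With all 188 LHWs as clusters (4160/188 = 22.1 children each), the design effect is 1 + (22.1 − 1) × 0.001736 = 1.037, giving about 1,904. That is a separate matter, and the percentages below do not depend on the total.

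**Step 1. Who has a value**

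| Arm and outcome | Children | SpO2 near the time of referral |
|---|---|---|
| Intervention, accepters | 2080 × 0.15 = 312 | yes, at home |
| Intervention, non-accepters | 2080 × 0.85 = 1,768 | yes, at home |
| Control, accepters | 2080 × 0.10 = 208 | yes, at hospital |
| Control, non-accepters | 2080 × 0.90 = 1,872 | none described |

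At 8% control acceptance the last row is 2080 × 0.92 = 1,914 children; at 23% it is 2080 × 0.77 = 1,602. So 77% to 92% of controls lack a value.

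**Step 2. Control-arm model**

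Among controls with a value, acceptance is 208/208 = 100%. The outcome does not vary, so a logit model for hypoxaemia cannot be fitted.

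**Step 3. Pooled complete-case model**

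- Children dropped: 1872/4160 = 45%, all control non-accepters.
- True overall acceptance: (312 + 208)/4160 = 520/4160 = 12.5%.
- Apparent acceptance: 520/(2080 + 208) = 520/2288 = 22.7%.
- Arm term: every remaining control is an accepter, so the term is perfectly separated. With it in the model, the other coefficients are in effect estimated from the intervention arm alone.

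**Step 4. Is the pooled hypoxaemia estimate biased if no arm term is fitted?**

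Assume no true effect within either arm, and set hypoxaemia prevalence at the ends of the 16% to 39% range.

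- Intervention 39%, control accepters 16%. Hypoxaemic: (121.68 + 33.28)/(811.2 + 33.28) = 0.1835. Not hypoxaemic: (190.32 + 174.72)/(1268.8 + 174.72) = 0.2529. Risk ratio 0.73.
- Intervention 16%, control accepters 39%: risk ratio 1.53.
- Equal prevalence: risk ratio 1.00.

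Now assume a true effect: intervention prevalence 20%, with acceptance of 20% in hypoxaemic and 13.75% in other children. The risk ratio is 1.45 and the odds ratio is (83.2/332.8)/(228.8/1435.2) = 1.57. Intervention accepters are 83.2/312 = 26.7% hypoxaemic.

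- If control accepters are also 26.7% hypoxaemic, they add 55.5 hypoxaemic and 152.5 other children. The odds ratio is (138.7/332.8)/(381.3/1435.2) = 1.57, unchanged, and the risk ratio is 1.40.
- If control accepters are 20%, 30% or 40% hypoxaemic, the risk ratio is 1.26, 1.47 or 1.69.

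The distortion can go either way and can be nil.

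**The case against.** **Refusers may be measured by community health workers.** The forms are in an appendix that is not shown, the secondary objective lists hypoxaemia among outcomes compared between accepters and refusers, and the Intervention delivery section says in general terms that LHWs and staff are trained on the oximeters. So a follow-up reading in refusers cannot be ruled out. It would not rescue the predictor, because it would come 24 hours or more after the decision and after the stat antibiotic dose. The general training sentence stands in the intervention section and does not override the statement that control children are assessed on signs alone. For the same reason, a reader might infer that the accept-versus-refuse comparison of hypoxaemia as an outcome should be dropped in controls. The documents do not support that: a later reading is legitimate for an outcome, and its absence from a condensed article does not show that it is not taken.

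**Model details belong to an analysis plan.** Whether models are pooled or fitted by arm, and how missing predictors are handled, can fairly be left there. If models are fitted by arm, the other predictors need not be affected. What stands is that the article commits to this predictor in both groups, and no analysis plan can supply data that the stated procedures do not collect.

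**A built-in spurious association.** A reader might infer that pooling must manufacture a link between hypoxaemia and acceptance. Step 4 shows that it need not. Recording unmeasured children as not hypoxaemic would create one, but nothing in the article proposes that coding.

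**The screening rule.** The plan also states that "The variables significant at a liberal p<0.20 will be included in multivariate model for adjustment". Some would object to univariate screening as such. It is a common choice, a separate question, and no part of this point.

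**Conclusion.** The point holds and should be fixed before analysis. As written, hypoxaemia cannot be estimated as a predictor of acceptance in the control arm: about 1,872 of 2,080 controls (90%) have no value and the remaining 208 or so are all accepters. A pooled complete-case model that includes it would discard 45% of the sample, show 22.7% acceptance in place of 12.5%, and leave any arm term inestimable.

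This rests on the planned acceptance rates, equal arm sizes, the definition of acceptance as including the hospital visit, and there being no control-arm reading before the decision other than those described. If families who agreed but did not arrive were counted as accepters, some accepters would lack a value too, but every control child with a value would still be an accepter.

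No size or direction of bias in a pooled hypoxaemia coefficient can be claimed, since both depend on prevalences that the article does not give. A reader might also infer that the trial's main comparison is compromised. It is not: the randomised comparison of acceptance between arms does not use SpO2 as a predictor. The gap concerns one of nine predictors in an associational objective, although the article labels that objective primary.

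**What to change.** State that hypoxaemia will be examined as a predictor of acceptance in the intervention arm only, using the LHW's household reading taken before the referral decision. Leave it out of control-arm and pooled predictor models, so that the other eight predictors are fitted on all children in both arms (4,160 children and about 520 expected acceptances at the planned rates). Amend the second primary objective or the predictor list to match.

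Two related clarifications would help. State whether community health workers take an SpO2 reading in refusers at any visit and, if so, that it serves as an outcome and not as a predictor. Reconcile the Intervention delivery section, which mentions handheld oximeters only for physicians at the centre serving intervention clusters, with Procedure at referral facility, which has oximetry for children arriving from either arm.

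The cost is a few sentences and no new data. The one loss is a control-arm estimate for hypoxaemia, which the stated procedures cannot supply.

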### Trial setting

The study will be conducted within the community of Taluka Kotri in District Jamshoro, Sindh (figure 2). Jamshoro District has a population of 993 142.^31^ It is predominantly rural, with 33% literacy, and >50% employed daily wage labourers. A baseline survey conducted as a part of current study showed the status of overall health indicators: skilled birth attendance 57%, antenatal care coverage 75%, postnatal care cover for mother and newborn within 48 hours 31.5%, vaccination completeness in children 12–23 months 68% and care seeking for ARI and diarrhoea >80% (internal survey). A total of 27 health facilities function in the district including 1 district headquarter (DHQ) hospital, 3 taluka headquarter hospitals, 5 rural health centres and 18 basic health units. The district is divided administratively in 30 union councils. Kotri is one of the four Talukas of Jamshoro, consists of 44% (437 561) of the population of district.^31^

**Figure 2 F2:**
[figure not shown]
Map of intervention and control sites Abbreviations used in Map: Liaqat University of Medical and Health Sciences Jamshoro (LUMHS). Legend: Lady Health Worker (LHW). Service Layer Credits: Companies/institutes which contributed and collaborated to make this basemap publicly available (Environmental Systems Research Institute (ESRI), HERE (private company), General Bathymetric Chart of the Oceans (GEBCO), US Geological Survey (USGS), Food and Agriculture (FAO), National Park Service (NPS), National Resources Canada (NRCan), GeoBase, Institut Geographique National (IGN), Ministry of Economy, Trade and Industry (METI).

Participants will be the permanent residents of Kotri, Jamshoro and recruited from their homes during routine monthly visits by LHWs serving in their catchment areas. This study is expected to run for 48 months with participant identification and enrolment conducted simultaneously in intervention and control clusters over 21 months after an initial pilot of 1 month. Each enrolled child will be revisited at day 7 and 14 for outcome measurement.

### Participant

Any child aged 0–59 months having signs and symptoms of acute respiratory illness (cough, fever, difficulty in breathing) in intervention clusters will undergo assessment of (1) signs and symptoms of severe pneumonia and (2) pulse oximetry during monthly LHW home visits. Presence of severe pneumonia with or without hypoxaemia, or hypoxaemia alone will merit hospital referral (non-facilitated). Any child aged 0–59 months having signs and symptoms of acute respiratory illness (cough, fever, difficulty in breathing) in control clusters will undergo assessment of (1) signs and symptoms of severe pneumonia alone. Presence of severe pneumonia will merit hospital referral (non-facilitated). Exclusion criteria will include lack of consent and, non-availability (lost to follow-up, migration) on days of scheduled follow-up visits (days 7 and 14). Those who accepted referral but did not show up at hospital will be included in final analysis.

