**Methods and analysis:**

A cluster randomised controlled trial using pulse oximetry as intervention for children with severe pneumonia will be conducted in community settings. Children aged 0–59 months with signs of severe pneumonia will be recruited by LHWs during routine visits in both intervention and control arms after consent. Severe pneumonia will be defined as fast breathing and/or chest in-drawing, and, one or more danger sign and/or hypoxaemia (Sa02 <92%) in PO (intervention) group and fast breathing and/or chest in-drawing and one or more danger sign in clinical signs (control) group. Recruits in both groups will receive a stat dose of oral amoxicillin and referral to designated tertiary health facility. Analysis of variance will be used to compare baseline referral acceptance in both groups with that at end of study.

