### Participant recruitment and study procedures

#### Intervention delivery

Children aged 0–59 months with cough and/or difficult breathing during regular home visits of LHWs will be assessed for first, signs and symptoms of severe pneumonia (fast breathing/chest in-drawing and one or more danger sign (unable to eat/drink, vomiting, convulsion and lethargy/unconsciousness) and/or stridor)) and second, hypoxaemia (SpO2 <92%) using a handheld pulse oximeter (Masimo Rad-5v) to measure blood oxygen saturation level. LHWs will also do case management of children with pneumonia and severe pneumonia. A 3-day course of oral amoxicillin will be given to children with pneumonia at home, whereas children meeting referral criteria (severe pneumonia alone, hypoxaemia alone or severe pneumonia and hypoxaemia) after obtaining informed consent (online supplemental appendix 2), will be administered a stat dose of oral amoxicillin and referred to nearest referral hospital (DHQ Kotri).

The study investigators will have provided these pulse oximeters to the LHW programme in advance and highlighted which ones will receive them. Physicians at the referral centre serving the intervention clusters will also receive handheld pulse oximeters. All the LHWs and staff will be trained on the use, and maintenance of these pulse oximeters. Children with severe pneumonia with or without hypoxaemia will be advised to go to hospital for antibiotics and oxygen, using the PO reading as a tool to convince parents. Children with hypoxaemia alone, without signs of severe pneumonia, will be referred to hospital to rule out cyanotic congenital heart disease. Name of the predesignated health facility with available oxygen and study physician will be provided to all the LHWs so that Study Workers (non-LHW study personnel) can coordinate with study physicians and ensure the patient has reached and is receiving safe and recommended care at referral facility. Project staff will pretest and regularly monitor PO accuracy and quality of readings.

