### Study status

Recruitment began in August 2019 and field activities and data collection are in process. As of 16 October 2020, a total of 235 cases and 184 controls have been enrolled. Extension of study duration is in discussion to achieve sample size.

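### Hypoxaemia alone qualifies a child only in intervention clusters, and the article's passages conflict on whether such children count in the primary acceptance rate

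*Protocol article*

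**What the plan says.** Study aims and design (protocol article) sets eligibility by arm. Intervention children are assessed for "study eligibility (signs and symptoms of severe pneumonia, or hypoxaemia alone, or severe pneumonia with hypoxaemia". For the other arm the text is: "In control areas, study eligibility will require detection of signs of severe pneumonia alone". The control procedure contains no household oximetry.

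Participant repeats the difference for referral. Intervention: "Presence of severe pneumonia with or without hypoxaemia, or hypoxaemia alone will merit hospital referral (non-facilitated". Control: "Presence of severe pneumonia will merit hospital referral (non-facilitated".

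The Abstract (Methods and analysis) builds it into the case definition. On top of fast breathing or chest in-drawing, the intervention arm needs "one or more danger sign and/or hypoxaemia (Sa02 <92%) in PO (intervention) group", whereas the control definition is "fast breathing and/or chest in-drawing and one or more danger sign in clinical signs (control) group".

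Intervention delivery gives the extra children their own reason for referral: "Children with hypoxaemia alone, without signs of severe pneumonia, will be referred to hospital to rule out cyanotic congenital heart disease".

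Data analysis describes the primary analysis as intention-to-treat, covering every enrolled child by allocated group. The primary objective and outcome (Study aims and design) and Sample size are all worded for children with severe pneumonia.

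**The concern.** The primary measure is a proportion: children whose families accept referral, divided by children enrolled. If enrolment in one arm depends partly on the oximeter reading, the intervention helps to decide, after randomisation, who is in the denominator. Randomising clusters does not protect that comparison.

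The additional children have no counterpart in the control arm. A control child with fast breathing and low saturation but no danger sign is not identified as hypoxaemic at home and does not enter the trial. There is no reason to expect the additional children to accept at the same rate as clinically severe cases: they look less ill, and those with hypoxaemia alone are referred for a different stated reason. An arm difference could therefore reflect who was enrolled rather than whether the reading changed a family's decision. It could equally mask a real effect.

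**Working it through.** **1. The passages side by side.**
- Pointing to inclusion of SpO2-only children in the primary comparison: the Abstract's arm-specific definition, and Data analysis (all enrolled children).
- Pointing to exclusion: the severe-pneumonia wording of the objective, outcome and sample size, together with Intervention delivery, which classes hypoxaemia-alone children as lacking those signs.
- The Abstract and the Methods also differ from each other. The Abstract requires fast breathing or in-drawing alongside hypoxaemia; Study aims and design, Participant and Intervention delivery accept hypoxaemia alone.

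The severe-pneumonia wording does not settle the matter, because the Abstract defines that term differently in each arm.

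**2. The plan's own sample size.** Inputs from Sample size, Data analysis, and Randomisation and masking: 10% v 15%, power 90%, alpha 5% (two-sided assumed), ICC 0.001736, 188 clusters (all assumed used).
- Per arm: [1.96·√(2·0.125·0.875) + 1.2816·√(0.10·0.90 + 0.15·0.85)]² / 0.05² = 918, total 1836.
- Mean cluster size 4160/188 = 22.1; design effect 1 + 21.1 × 0.001736 = 1.037.
- Total 1836 × 1.037 = about 1903.

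The stated 4160 does not reproduce from these inputs. The article gives neither cluster size nor an attrition allowance, so this does not show that 4160 is wrong. It is a separate matter, and 4160 is used below as the planned size.

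**3. Size of the distortion.** Let f be the SpO2-only share of intervention enrolments, q their acceptance, and p the acceptance of clinically severe cases in that arm. The arm shows (1 − f)p + fq, so the shift is f(q − p). It contains no sample size and is zero only if q = p (or f = 0). Neither f nor q is in the article; both are assumptions. The Introduction's 16–39% community hypoxaemia prevalence is a different quantity from f. Its 8–23% acceptance figure concerns facilitated referral of sick young infants, so it is only a loose guide to q.

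Effective size per arm: 2080/1.037 = about 2006.

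*No oximetry effect (p = 10%, control 10%).* Probability of a significant two-sided result:

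| f | q = 5% | q = 10% | q = 15% | q = 20% | q = 30% |
|---|---|---|---|---|---|
| 10% | 8% | 5% | 8% | 18% | 53% |
| 20% | 19% | 5% | 18% | 53% | 97% |
| 30% | 38% | 5% | 34% | 85% | about 100% |

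Worked cell, f = 20%, q = 20%: rate 0.8 × 10% + 0.2 × 20% = 12%. Standard error √(2 × 0.11 × 0.89/2006) = 0.00988. (0.02 − 1.96 × 0.00988)/0.00987 = 0.065, giving probability 0.53. At q = 20% the arm shows 11%, 12% and 13% for f = 10%, 20% and 30%. At q = 5% the spurious difference mostly runs against oximetry.

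*True effect as planned (p = 15%, control 10%).* Power at 4160:

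| f | q = 5% | q = 10% | q = 15% |
|---|---|---|---|
| 10% | 97% | 99% | 99.8% |
| 20% | 85% | 97% | 99.8% |
| 30% | 53% | 93% | 99.8% |

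For q = 5% the arm shows 0.8 × 15% + 0.2 × 5% = 13% at f = 20%, and 0.7 × 15% + 0.3 × 5% = 12% at f = 30%.

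**4. With one definition in both arms (f = 0).** The contrast returns to 10% v 15%, the false-positive rate to 5%, and power at 4160 to about 99.8%.

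**The case against.** The best defence is the article's own wording. The question is put for children with severe pneumonia, and hypoxaemia-alone children are said to lack its signs. On that reading they are enrolled and referred but lie outside the primary outcome, and an analysis plan not shown may say so. This stands as a possible reading, but the Abstract and Data analysis contradict it, and eligibility is something the protocol itself fixes.

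A second defence is that finding more children is part of the strategy. That is a legitimate aim and fits the overall aim as worded, but a proportion among those detected does not measure it; it needs a denominator that detection cannot change.

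Two stronger inferences are tempting and are not supported.
- A reader might conclude that the trial cannot answer its primary question. The signs are assessed first and SpO2 second in Intervention delivery, so a common analysis set may be recoverable, and one reading of the text already implies it.
- A reader might take the Study status count, "a total of 235 cases and 184 controls have been enrolled", as proof of wider entry (235/184 = 1.28, taking cases and controls to mean the two arms). The count is compatible with that but is not evidence of it. Treating children as independent gives z = 25.5/√(419 × 0.25) = 2.49. This drops below 1.96 once the count variance is (2.49/1.96)² = about 1.6 times Poisson. With 419/188 = 2.2 children per cluster, a between-cluster coefficient of variation of about 0.53 is enough. Varying catchments, pandemic disruption, incentives and the extra training in one arm are other explanations found in the article. Nothing ties the excess of 51 to SpO2-only children.

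**Conclusion.** The point holds, and the plan needs correction here. Entry criteria differ by arm, the case definition differs by arm, and the analysis as written counts everyone enrolled. The passages that would keep SpO2-only children out of the primary comparison conflict with those that put them in.

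Against a planned difference of only 5 percentage points, a shift of 1 to 3 points is material, and it can run in either direction. How large it is in this trial cannot be known from the article: every figure for false-positive probability and power depends on the assumed f and q, on use of all 188 clusters, and on a two-sided 5% test. The conclusion that the groups are differently composed depends on none of these.

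**What to change.** Define the primary analysis set in both arms as children who meet the clinical-sign definition that Intervention delivery and Implementation of active control already share, classified before the SpO2 reading. Reconcile the Abstract's definition, the primary outcome paragraph and Data analysis with that set. Report intervention children who qualify only on SpO2 separately and descriptively. Leave the referral and management rules in Participant and Intervention delivery unchanged; only the analysis set moves.

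Hospital arrivals with an LHW referral slip per 1,000 under-5 children per cluster may be added as a secondary analysis of the whole strategy. It is a different estimand, since wider referral alone can raise it, and should not be presented as a robustness check of acceptance.

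Costs:
- SpO2-only children stop counting toward the primary sample. At 2080 per arm and f = 30%, 0.7 × 2080 = 1456 intervention children remain, against about 1903/2 = 952 per arm for 90% power on the stated inputs. Recruitment stood at 419 in October 2020, so the loss would lengthen an already delayed study if 4160 remains the target.
- The data forms, which are not shown, must be checked to confirm that signs were recorded independently of SpO2.
- Unblinded LHWs still classify the signs, and one group has oximeters and extra training. A common definition reduces this source of bias but does not remove it, and the report should say so.
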